Earlier studies showed that the length of the common channel plays a role in the outcome of surgery both in weight loss and in micronutrient deficiencies. The length of the total small bowel can vary considerably with measured values between 350 to more than 1000 cm (5).

In this study of Tacchino in 443 patients TSB median length was 690 cm (women 678±92, men 728±85 cm) with a SD of 94 cm. In males 3% had a bowel length < 400 cm and 15% > 800, in females 2% had a length of < 400 cm and 5% > 800 cm.

In current practice in OLGB surgery surgeons use a fixed BP-limb length or adjust the length to the initial BMI. Total weight loss varies in literature between 30-35 % with SD up to 8.5%, aiming at a BMI result between 23 and 30 Kg/m^2^

The contribution of the length of the residual small bowel, total minus the BP-limb, on weight loss and deficiencies has up till now not been studied in OLGB surgery.

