12) To compare the proportion of patients between the groups at 1, 2, 3, 4 and 5 years with remission of hypertension, defined as a blood pressure of 140/90 mmHg or less without antihypertensive medication ^#^.

13) To compare the proportion of patients between the groups at 1, 2, 3, 4 and 5 years with improvement of hypertension, defined as a lower blood pressure of at least 10 mm Hg systolic and/or 5 mmHg diastolic, and/or less antihypertensive medication (not reaching the criterion of remission) ^#^.

14) To compare the proportion of patients between the groups at 1, 2, 3, 4 and 5 years with resolution of sleep apnea, defined by cessation of CPAP or other devices use, documented by their own pulmonologist

15) To perform analysis of the above parameters in the subgroups with TSBL 500-700 and >700.

16) To compare within the standard group of patients with an allocated BP-limb length of 150 cm those with a TSBL < 500 to those with a TSBL 500-700 and to those with TSBL >700 cm on the above mentioned parameters.

^#^ : patients are asked to bring along with their visit an overview of current medication from their local pharmacist and actual use will be checked with the patient. In case of absence of the overview, after informed consent is given, the local pharmacist will be asked to provide the investigator with an overview of the medication

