## Sample size calculation

The null hypothesis in the study is as follows : the percentage TWL at five years in both groups is not different with a mean of 35. The alternative hypothesis is that the mean of the absolute difference in TWL in the experimental group is 5% more than the standard group (40% and 35% respectively).

For the evaluation of the primary endpoint of the percent total weight loss (%TWL) at five years, a sample size of 2x 92 will achieve 80% power to detect a (absolute) difference of -5.0% between the null hypothesis ( both group means of %TWL are 35.0) and the alternative hypothesis (mean of experimental group is a %TWL of 40.0) with estimated group standard deviations of 12.0 and 12.0 and with a significance level (alpha) of 0.05 using a two-sided two-sample t-test.

In case of a reduced standard deviation in the active treatment group of 9.0, the power achieved is 88.8%.

With an expected maximum drop-out due to conversion of OAGB to RYGB of 15% the sample size is 92 plus 14 = 106 patients in each group, leading to a total of 212 participants in the study.

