## For qualitative parameters (categorical or ordered), frequency counts and percentages of each category will be calculated by treatment group. Percentages will be reported up to 1 decimal place.

## Primary study parameter(s)

The primary null hypothesis for this study is that there is no significant difference in the mean change in the percent of total weight loss (%TWL) at five years, between patients treated with a TSBL adjusted BP limb length (active group) versus patients treated with a standard BP limb length of 150 cm (control group).

In addition to the descriptive statistics (see the above section : Patient demographics other baseline characteristics), the two treatment strategy groups will be compared using two-sample T-test if parameter is normally distributed. Visual inspection of the distribution, as well as the Shapiro-Wilk test for normality, will used to assess normality. Unless equality of variance between groups is established, the Satterthwaite method for t-statistics and 95% confidence intervals will be used. If data is skewedly distributed, a Mann-Whitney U-test (Wilcoxon two-sample test) will be applied. For the difference in medians, the Hodges-Lehmann estimate will be used with distribution-free 95% confidence intervals.

In addition to the above mentioned analyses, the homogeneity of treatment effect over different strata of patients will be evaluated. In this, differences in treatment effect over separate strata of potentially relevant factors (e.g. gender, baseline BMI, co-morbidities, compliance, etc) will be evaluated. A multivariable model will be used to formally establish homogeneity, i.e. the absence of effect modification for the potentially relevant factors, separately.

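### Secondary objective 16 rests on a bowel-length class of about two to five patients, and the effect-modification analysis claims a homogeneity that this sample cannot establish

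*Protocol*

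**What the plan says.** The last item under Secondary Objective(s), number 16, takes only patients allocated to the 150 cm limb. It sets "those with a TSBL < 500 to those with a TSBL 500-700 and to those with TSBL >700 cm" on all parameters listed before it. Item 15, directly above, plans analyses in the 500-700 cm and >700 cm subgroups and leaves the shortest class out.

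The Introduction reports, from a cited series of 443 patients, "TSB median length was 690 cm (women 678±92, men 728±85 cm) with a SD of 94 cm". It also gives shares in the lower tail: "In males 3% had a bowel length < 400 cm" and "in females 2% had a length of < 400 cm".

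The Sample size calculation states that "a sample size of 2x 92 will achieve 80% power" for a 5-point difference with SD 12, and that with drop-out "the sample size is 92 plus 14 = 106 patients in each group".

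Under Primary study parameter(s) in the Statistical Analysis chapter, treatment effects are to be examined across strata of factors given as "e.g. gender, baseline BMI, co-morbidities, compliance, etc". The stated aim is: "A multivariable model will be used to formally establish homogeneity, i.e. the absence of effect modification".

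**The concern.** Two things that the protocol itself fixes look unsound.

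First, objective 16 makes the shortest-bowel class the group against which both other classes are set. The protocol's own bowel-length figures suggest that this class will be almost empty. The objective matters because limb length is constant in the standard arm, so differences between classes there reflect bowel length without the adjustment rule. The Introduction names the role of residual bowel length as an open question in this operation.

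Second, an interaction test in a trial sized for a main effect cannot show that an interaction is absent. If the stated aim is followed, a non-significant result could be read as evidence of uniform benefit. The factor list also includes compliance. This is counted from returned capsules during follow-up (Drug accountability), so it arises after randomisation and may itself respond to the allocated operation.

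**Working it through.** **Reproducing the plan's own figure.** Inputs: difference 5, SD 12, two-sided alpha 0.05, power 80%. The normal formula gives n = 2 × (1.96 + 0.8416)² × 12² / 5² = 90.4, so 91 per arm. The exact t-test gives 79.8% power at 91 and 80.3% at 92. The stated 92 is confirmed, and 92 × 1.15 = 105.8 gives the stated 106. The sample size is not at issue.

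**Expected number below 500 cm in the standard arm.**
- Normal model, centre 690, SD 94: (500 − 690)/94 = −2.02, so P = 2.16%. That is 2.0 of 92 or 2.3 of 106, with a 13% or 10% chance of no such patient. The binomial 95% range is 0-5 or 0-6.
- The normal model is too thin in the lower tail: it puts 0.1% below 400 cm, where the Introduction reports 2% to 3%. The share of women implied by the figures is (728 − 690)/(728 − 678) = 0.76. The reported share below 400 cm is then 0.76 × 2% + 0.24 × 3% = 2.24%, or 2.1 of 92 and 2.4 of 106, before anyone at 400-500 cm is counted.
- Adding the sex-specific normal share for 400-500 cm (2.10% − 0.10% = 2.0%) gives about 4.25%, or 3.9 of 92 and 4.5 of 106.

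The working range is about 2 to 5, with 2 as the floor.

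**Precision of <500 against 500-700 cm.** The normal model puts 52.1% in 500-700 cm, about 48 of 92. Half-width = t × 12 × √(1/k + 1/48), with k the number below 500 cm:

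| k | Standard error | 95% half-width | Power for 5 points | Detectable at 80% power |
|---|---|---|---|---|
| 2 | 8.66 | 17.4 | 9% | about 25 |
| 5 | 5.64 | 11.3 | 14% | about 16 |

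Using 106 (55 in the middle class) changes the half-widths only to 17.3 and 11.2. Even 8 patients would leave ±9.2. For binary outcomes, one patient moves the proportion by 1/5 = 20 percentage points when k = 5, and by 1/2 = 50 when k = 2.

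**What the standard arm can show.**
- 500-700 against >700 cm, about 48 against 42 of 92: standard error 12 × √(1/48 + 1/42) = 2.54, half-width 1.99 × 2.54 = 5.0 points.
- Bowel length as a continuous variable in about 90 patients: 80% power at r = tanh(2.80/√87) = 0.29, which is 0.29 × 12 = 3.5 points of %TWL per 94 cm.

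**Interaction test.** For a factor split 50/50, the standard error is 4 × 12/√N.
- N = 184: 3.54; power for a 5-point interaction 29%; detectable at 80% power 2.80 × 3.54 = 9.9 points.
- N = 212: 3.30; power 33%; detectable 9.2 points.

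For the 500-700 and >700 cm classes the standard errors are 3.58 and 3.34, with power 29% and 32%. An observed interaction of zero at N = 184 would have a 95% interval of ±1.96 × 3.54 = ±6.9 points, wider than the whole design effect. No margin is stated against which such an interval could be judged.

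**The case against.** Several points on the other side stand.

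- The median and SD alone suggest two patients, and a reader might take that as the protocol's prediction. The same paragraph's shares below 400 cm make two a floor.
- A reader might infer that the bowel-length question would be answered by a handful of patients. That goes too far. The other two classes hold about 95% or more of the arm, their data are collected, and their contrast is informative. Nothing excludes it, although the sentence does not ask for it.
- A reader might infer that bowel length is ignored as an effect modifier. It is not. Objective 15 plans subgroups by bowel length, and the factor list is openly illustrative. Naming every interaction term is commonly left to an SAP. The residue is narrow: objective 15 states no interaction test, and separate subgroup results do not test whether effects differ.
- The section gives no rule equating non-significance with homogeneity, so it cannot be said that a null test will be reported as proof. The stated aim still claims more than the sample allows. The Secondary study parameter(s) section is more careful about side effects: it relies on confidence intervals and declines formal non-inferiority tests because of sample size.
- The adjusted arm follows a step rule, so classes suit between-arm comparisons better than a straight line. Within the standard arm limb length is constant, so this argument does not apply to objective 16.

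The interim look after 50 patients does not rescue objective 16. It counts short bowels only among patients allocated to the intervention, and for study power.

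**Conclusion.** The point holds in limited form. The <500 cm comparison in objective 16 cannot support inference: about 2 to 5 patients, ±17 to ±11 points of %TWL, and 9% to 14% power for a 5-point difference. The homogeneity aim cannot be met: 29% to 33% power for an interaction as large as the whole treatment effect, about 9 to 10 points detectable at 80% power, and no margin. Compliance does not belong in the list as a modifier. The absence of bowel length from that list is a lesser matter.

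The figures assume that the cited series represents this trial's patients, a normal shape outside the reported tail, SD 12 within every class, and an even split for the generic interaction. The count below 500 cm is uncertain, but the conclusion is the same at 2, 5 or 8 patients. The primary comparison and the sample size are not affected.

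**What to change.** **Objective 16.** Analyse each outcome in the standard arm on bowel length as a continuous variable, with linearity checked, for example by a spline. Compare 500-700 with >700 cm. Report the <500 cm class descriptively only.

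**Primary study parameter(s).** Replace the aim of establishing homogeneity with estimates of each interaction and their 95% confidence intervals. Remove compliance as an effect modifier. Include an arm-by-bowel-length interaction using the two classes of objective 15, with continuous bowel length as supportive. Bowel length is a legitimate modifier: under the randomisation section it is measured before the envelope is opened.

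**Cost.** Wording only. Bowel length is already recorded for every patient, and no extra patients or visits are needed. The price is a linearity assumption to check and a weaker, but supportable, statement about consistency of effect.

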**Objective**:

Primary :

To compare the percent total weight loss (%TWL) at 5 years between the group with the standard BP-length and the group with an adjusted BP-length.

Secondary :

To compare the proportion of patients with a BMI between 22 and 30 Kg/m^2^,the mean number of daily bowel movements and number of days with daily bowel movements > 3 over in the last two weeks before a visit, Quality of life measured by the RAND-36 questionnaire between the groups and the percentage of patients experiencing moderate to severe dumping symptoms defined by the Dumping Severity Score (DSS) between the groups.

To compare the proportion of patients in the two groups who have neither deficiencies of iron, nor vit. D, nor vit B12 without extra suppletion, during the study

**Study design:** double blind intervention study

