**Secondary Objective(s):**

1) To compare the percent of total weight loss (%TWL) between the groups at 1,2,3 and 4 years.

2) To compare the percent excess weight loss (%EWL) between the groups at 1,2,3, 4 and 5 years.

Definition: %EWL (Initial Weight – Postop Weight) / (Initial Weight – Ideal Weight)

(ideal weight is defined by the weight corresponding to a BMI of 25 kg/m2 )

3) To compare the percent excess BMI loss (%EBMIL) between the groups at 1,2, 3, 4 and 5 years.

Definition: %EBMIL (ΔBMI / (Initial BMI – 25)) * 100)

4) To compare the proportion of patients with 22 ≤ BMI ≤ 30 between the groups at 1,2 3, 4 and 5 years.

5) To compare the mean number of daily bowel movements and number of days with daily bowel movements > 3 in the last two weeks, between the groups at 6 months, 1,2, 3, 4, and 5 years.

6) To compare the Quality of life measured by the RAND-36 questionnaire between the groups at 6 months, 1,2, 3, 4 and 5 years, absolute and compared to before surgery

7) To compare the percentage of patients experiencing moderate to severe dumping symptoms defined by the Dumping Severity Score (DSS) (see Emous et al.) at 6 months, year 1, 2, 3, 4 and 5 between the groups, absolute and compared to before surgery.

8) To compare the proportion of patients in the two groups who have neither deficiencies of iron, nor vit. D, nor vit B12 without extra suppletion, at 6 months, 1, 2, 3, 4 and 5 years. Deficiencies are defined by the lower border of the local normal laboratory values.

9) To compare the proportion of patients in the two groups who have a deficiency at 6 months, 1, 2, 3, 4 and 5 years, or received extra suppletion for :

- Vitamin B1

- Vitamin B6

- Folic acid

- Vitamin A

- Vitamin D

- Calcium

- Phosphate

- Albumin

- Zinc

- Copper (visit 1,3,5 years)

- Selenium (visit 1,3,5 years)

Deficiencies are defined by the lower border of the local normal laboratory values.

10)To compare the proportion of patients between the groups at 1, 2, 3, 4 and 5 years without diabetes, both those with remission of diabetes and those without de novo diabetes, defined as an HbA1c less than 48 mmol/mol without diabetes medication in the last 6 months. ^#^

11) To compare the proportion of patients between the groups at 1, 2, 3,4 and 5 years with improvement of diabetes, defined as a reduction of HbA1c with at least 10 mmol/mol, but not reaching remission criteria and/or less anti-diabetic medication ^#^.

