# STUDY POPULATION

## Population : patients from the Centrum Obesity North-Netherlands (CON), who comply with the IFSO criteria during a multidisciplinary screening and have chosen to have a primary mini-GB (OLGB) and are willing to participate.

## Inclusion criteria

In order to be eligible to participate in this study, a subject must meet the following criteria:

- Age between 18 and 65
- BMI > 40 kg/m^2^ or
- BMI > 35 kg/m^2^  with co-morbidity : diabetes, hypertension, OSAS, arthrosis
- Willing to participate with written informed consent before start of the surgery
- A completely measured total small bowel during surgery
- No pre-operative deficiencies of vit B_12_, vit D and iron, measured with ferritin
- No use of extra (multi-)vitamin supplements with exception of vit D max 800 IU/day
- Able to swallow the multivitamin FFM WLS primo (tested before surgery)

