## Study procedures

A standard operation protocol for OLGB will be used in all patients. The pouch will be made with the help of a linear stapler. At first, the stomach will be transected horizontally at the junction of the corpus and antrum at the level of crow’s foot. A small pouch is made with help of a calibration sonde of 34 French, the pouch is finished near the angle of His. Then the total limb length is measured. With a succesfull TSBL measurement the OR nurse will open the envelop and the allocated procedure will be communicated to the surgeon. Based on the randomization outcome biliopancreatic limb length is measured. In case the measurement of the total limb length does not succeed, standard limb length of 150 cm is performed. An antecolic, retrogastric anastomosis is performed by liniar stapling and the remaining defect is closed by V-loc. An anti-reflux stitch is performed. Integrity of the anastomoses is checked by methylene-blue-test and in case of leakage, extra sutures will be applied. The mesenterial defect of Peterson will be closed as far as possible by endo hernia stapling or unresolvable V-loc.

The extra measurements of limb length will take less than ten minutes of time. In patients allocated to standard treatment the surgeon will construct a BP-limb of 150 cm. In patients allocated to the adjustment length, the length of the BP-limb will depend on the total small bowel length : < 500 cm : 150 BP; 500-700 cm : 180 BP and > 700 cm : 210 BP.

On leave of the hospital the patients will be provided with Fitforme WSL Primo multivitamin capsules for the following period and will be instructed to use one capsule once daily.

Follow-up will take place in accordance with usual care, i.e. after 1,6,12 and 24 months and yearly up till 5 years. Extra visits will be at 18,30,42 and 54 months for compliance check and distribution of FFM multivitamins.

Weight measurements and blood samples will be taken in accordance with the standard protocol of follow-up after bariatric surgery in our institute added with 20 ml for selenium and copper measurements and future lab tests at 1,3 and 5 years.

Data from 6,12 and 24 months and every year thereafter up to five years after surgery will be anonymously collected in a database.

At each visit standard care includes :

- inquiry after well being and complaints, side effects, adverse events
- documenting current medication use, both regular and over-the-counter, and when applicable CPAP use

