- inquiring after co-morbidities
- measurement of body weight, blood pressure and pulse
- drawing of blood samples for routine post operative care including :

CRP, hemoglobin, WBC, thrombocytes, sodium, potassium, creatinin, BUN, ASAT, ALAT, alkaline phosphatase, yGT, HbA1c, glucose, calcium, magnesium, phosphate, albumin, vit B_1_, vit B_6_, vit B_12_, folic acid, ferritin, vit A, vit D, Zinc

- Scheduling a new appointment

If the patient forgot to bring along a recent overview of current medication from their own pharmacy , the actual medication use will be requested from the local pharmacy.

Extra effort for the patient in the study includes :

- Bringing along a written overview of current medication from the local pharmacy to the appointment.
- Bringing back all used and non-used blisters and boxes for counting of compliance of the use of the FitForMe WLS primo pills
- filling in the DSS questionnaire
- filling in the RAND 36 questionnaire
- drawing of 20 ml of extra blood during the venepuncture for selenium, copper and storage for later investigations at 1,3 and 5 years
- Visits at 18, 30,42, and 54 months for counting left over pills and distributing new ones for the forthcoming 6 months

All patients will be treated with 800 IU vitamin D and 500 mg Calcium in a combination pill as part of standard care.

In case of deficiencies of vitamins or micronutrients they will be substituted according to standard care.

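### Secondary endpoint 10 looks back 6 months for diabetes drugs, but its named source is current medication only; endpoints 8 and 9 lack one consistent suppletion window

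*Protocol*

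**What the plan says.** **Endpoint 10 (diabetes).** Section 2, secondary objective 10, and its counterpart in Section 7.1.2 count patients without diabetes at 1, 2, 3, 4 and 5 years, "defined as an HbA1c less than 48 mmol/mol without diabetes medication in the last 6 months". Footnote # in Section 2 is attached to objectives 10 to 13 and gives the source: "patients are asked to bring along with their visit an overview of current medication from their local pharmacist". Actual use is then checked with the patient. If the overview is missing, the pharmacist is asked for one. Section 7.3 lists, for each visit, "documenting current medication use, both regular and over-the-counter, and when applicable CPAP use", and repeats the request for a pharmacy overview of current medication.

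**Visits.** Section 7.3 sets usual-care visits at 1, 6, 12 and 24 months and then yearly to 5 years. Extra visits at 18, 30, 42 and 54 months are described as being for capsule counts and distribution. The data listed for the database are those of month 6, month 12, month 24 and each year after that.

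**Endpoints 8 and 9 (deficiencies).** The Summary compares patients with no deficiency of iron, vitamin D "nor vit B12 without extra suppletion, during the study". Section 2 instead takes those "who have neither deficiencies of iron, nor vit. D, nor vit B12 without extra suppletion, at 6 months, 1, 2, 3, 4 and 5 years", and Section 7.1.2 also ties the endpoint to those visits. Endpoint 9 counts patients who have a deficiency at a visit or who *received* extra suppletion, with no period given. Section 7.3 has deficiencies substituted under standard care and also states: "All patients will be treated with 800 IU vitamin D and 500 mg Calcium in a combination pill as part of standard care".

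**The concern.** An endpoint defined over a period needs data over that period. Endpoint 10 asks about 6 months, while the record that the protocol prescribes describes the day of the visit. A patient with HbA1c below 48 mmol/mol who came off a diabetes drug two months earlier shows no current drug and would be scored as diabetes-free, although the definition says otherwise. An analysis plan cannot repair this later, because the dates would not have been collected.

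For endpoints 8 and 9 the problem is mainly one of definition. Whether a supplement course that ended before a visit counts at that visit depends on which part of the protocol is followed. If past courses do count, a record of current use cannot show those begun and finished between visits. This matters because the Introduction and Section 5 report more micronutrient deficiencies with a longer BP-limb, and Section 9 (safety analysis) moves non-serious nutrient deficiencies into the secondary efficacy endpoints.

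**Working it through.** The protocol gives no figure of its own to reproduce here. The check is which planned time points fall in the look-back window, and how the definitions compare.

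**Inputs (Section 7.3; window from objective 10).** Database time points: 6, 12, 24, 36, 48, 60 months. Extra visits: 18, 30, 42, 54 months. Window for an assessment at month v: from v − 6 up to v.

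| Assessment v | Window starts (v − 6) | Earlier database point in window | Earlier visit in window, extra visits included |
|---|---|---|---|
| 12 | 6 | 6 (on the edge) | 6 (on the edge) |
| 24 | 18 | none | 18 (on the edge) |
| 36 | 30 | none | 30 (on the edge) |
| 48 | 42 | none | 42 (on the edge) |
| 60 | 54 | none | 54 (on the edge) |

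**Database list only.** Take a patient on a drug at month 12 and off it at month 24. The stop lies somewhere in a gap of 24 − 12 = 12 months, twice the 6-month window. A stop at month 15 satisfies the definition and a stop at month 20 does not, but the two leave identical records. Scored on current use at month 24, both are diabetes-free if HbA1c is below 48 mmol/mol.

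**Extra visits also recorded.** A patient on a drug at month 18 and off it at month 24 could be recognised if the two readings were combined, although the protocol does not say to do this and the month-18 reading sits on the boundary. A drug started and stopped strictly between months 18 and 24 remains invisible. Month 12, with its month-6 reading, is in the same position.

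**Endpoints 8 and 9 side by side.**
- Endpoint 8, Summary: no extra suppletion over the whole study. One course at any time disqualifies the patient from then on.
- Endpoint 8, Sections 2 and 7.1.2: status at each visit. A patient deficient at month 12, substituted, and replete and off supplements at month 24 counts as deficiency-free at month 24.
- Endpoint 9, Sections 2 and 7.1.2: suppletion received, with no start of the period stated.

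The same patient at month 24 fails endpoint 8 under the Summary and passes it under Sections 2 and 7.1.2. Under endpoint 9 the score is undetermined.

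**The case against.** The strongest reply is that the medication record is more than a snapshot. Use is checked with the patient, the footnote's fallback request to the pharmacist is not worded as limited to current drugs, and the record is made at each visit, which may include the 6-monthly extra visits. Dates and look-back questions could also sit in the case report form. This stands in part: some stopped drugs will come to light. But none of these provisions requires a history or dates, and the protocol itself specifies current medication as the source for an endpoint with an explicit 6-month condition.

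For endpoints 8 and 9 the reply carries more weight. Footnote # does not cover them. Under the at-visit wording of Sections 2 and 7.1.2, a course that has ended is not an error. Only the Summary wording, or endpoint 9's open-ended *received*, makes it one.

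Three stronger readings are tempting, and the documents do not support them:
- A reader might infer that finished courses hide a true difference in deficiencies between the arms. Blood values are measured at every data visit, so a deficiency present at a visit is counted at that visit. Any figure for later dilution would need deficiency rates by arm and course lengths, which the protocol does not give.
- A reader might set the eligibility criterion "No use of extra (multi-)vitamin supplements with exception of vit D max 800 IU/day" beside the vitamin D and calcium pill given to everyone, and infer that nobody can meet endpoint 8 and that everybody meets endpoint 9 for those nutrients. The criterion governs entry before surgery and does not define an endpoint. Section 7.3 also separates the common pill from substitution of deficiencies. The ordinary meaning of extra is beyond what all patients receive.
- A reader might extend the point to objectives 11 to 13, which share the footnote. Those objectives state no look-back period, so no mismatch is shown.

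**Conclusion.** The point holds for endpoint 10. Followed as written, the protocol collects current medication for a definition that needs 6 months of history. At months 24, 36, 48 and 60 no earlier database time point falls inside the window. At month 12 the only one, month 6, lies on its edge. A drug stopped inside the window can be scored as absence of diabetes, so the error runs towards too many patients counted as diabetes-free.

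For endpoints 8 and 9 the point is narrower: the Summary conflicts with Sections 2 and 7.1.2 on the period for endpoint 8, endpoint 9 has no period, and a current-use record could not support a look-back if one is intended.

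The number of patients affected and the direction of any effect on the comparison between arms cannot be computed from the documents. The conclusion assumes that no other document already requires dated medication histories. It concerns secondary endpoints only. The primary endpoint, %TWL at 5 years, is untouched.

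**What to change.** - **Endpoint 10.** In footnote # of Section 2 and in Section 7.3, replace the overview of current medication, for this endpoint, with a pharmacy medication or dispensing history with dates covering at least the previous 6 months. State that endpoint 10 is scored on that history.
- **Endpoints 8 and 9.** Choose one suppletion window and use it in the Summary, Section 2 and Section 7.1.2. If it looks back, record supplements, including over-the-counter products, used since the previous data visit. If status at the visit is meant, remove the whole-study wording from the Summary and word endpoint 9 to match.
- **Definition.** For clarity, state that the study multivitamin and the vitamin D and calcium pill given to all patients are not extra suppletion.

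These changes affect recording and scoring only, not patient care. The cost is protocol wording and slightly more data entry. The local pharmacy is already the named source, either through the patient's overview or by direct request when that is missing, so what changes is the period covered. Reported diabetes-free rates may be slightly less favourable.
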